## Oversight and monitoring

### Composition of the coordinating center and trial steering committee {5d}

Not applicable.

### Composition of the data monitoring committee, its role and reporting structure {21a}

This clinical trial will not include a data monitoring external committee because it includes therapies widely used by pelvic physical therapists as well as assessments commonly applied among rectal cancer patients. Nonetheless, we will establish an internal committee for monitoring preliminary data regarding safety. This committee will include the researchers that assess the main outcomes and the main researcher. They will perform constant preliminary data analysis looking for safety and effectiveness. In case of any reported adverse event, this committee will ask for analysis and recommendation of an external surgeon with expertise in treating rectal cancer. Data monitoring group is independent from the funder and sponsor.

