## Assignment of interventions: blinding

### Who will be blinded {17a}

The people assessing the outcomes and those analyzing the results/data will be blinded.

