### Data management {19}

Data will be tabulated in an Excel sheet anonymously using codification by a research assistant. Control and experimental group will be coded anonymously with numbers (1, 2) aiming to blind the person who will perform statistical analysis. Data will be stored in the secured network of Universidad Bernardo O´Higgins with access to the researchers and, for security reasons, in an external hard drive which will be used to back up regularly the database. The data monitoring team will be the researcher that assesses outcomes and another responsible for data analysis.

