### Interim analyses {21b}

Not applicable.

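### Interim analyses are declared not applicable, yet a safety committee that includes the blinded assessors is to analyse effectiveness throughout, which threatens assessor blinding and leaves the 5% error rate unprotected

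*Protocol article*

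**What the plan says.** Five statements in the protocol article bear on this point.

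- Interim analyses {21b}: "Not applicable".
- Composition of the data monitoring committee {21a}, on the remit: "we will establish an internal committee for monitoring preliminary data regarding safety".
- The same section, on membership and task: "This committee will include the researchers that assess the main outcomes and the main researcher". Then: "They will perform constant preliminary data analysis looking for safety and effectiveness".
- Who will be blinded {17a}: "The people assessing the outcomes and those analyzing the results/data will be blinded".
- Data management {19}, on masking: "Control and experimental group will be coded anonymously with numbers (1, 2) aiming to blind the person who will perform statistical analysis". On the monitoring group: "The data monitoring team will be the researcher that assesses outcomes and another responsible for data analysis".

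Statistical methods {20a} applies a threshold of p < 0.05 to every test. No section gives a number of effectiveness looks, a boundary, an alpha allocation, or a rule by which an effectiveness result could stop or alter the trial.

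**The concern.** Comparing effectiveness on accumulating data is an interim analysis, whatever it is called. The protocol rules such analyses out in one section and prescribes them, without limit, in another. An analysis plan could not make both statements true.

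Two things are at stake. The first is the blinded evaluator, a named feature of the design; {17a} lists neither patients nor therapists as blinded. Under {18a} one researcher assesses outcomes at baseline and at follow-up visits, and another performs manometry. If the same people watch results build up, they carry that knowledge into the assessments still to come, and assessor bias cannot be removed in the analysis afterwards.

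The second is the false-positive rate. Unlimited looks at an unadjusted 0.05 offer no protection if anyone acts on one of them.

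**Working it through.** **1. Sections side by side**

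| Question | One section | Another section |
|---|---|---|
| Are there interim analyses of effectiveness? | {21b}: no | {21a}: yes, continually |
| What is the committee for? | {21a}, when introduced: safety | {21a}, later: safety and effectiveness |
| Who monitors? | {21a}: outcome assessors and main researcher | {19}: outcome assessor and data analyst |
| May assessors learn the allocation? | {17a}: no, they are blinded | {21a} and {19}: they sit on the body that examines the data |

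**2. Could coded data reveal the arm?** The 1/2 coding in {19} is aimed at the person who does the statistical analysis. {21a} does not say whether the committee sees pooled data, data by coded group, or data by named group. If it sees coded groups, a clear difference in bowel scores invites a guess at which code is the rehabilitation arm. Adverse events may also hint at it: {22} times their assessment by pre-rehabilitation and rehabilitation, which controls do not receive during the study ({11d}). This is inference about what could happen; the documents do not say that it will.

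**3. The plan's own sample size is a single-look design.** Inputs from Sample size {14}: means 2.8 and 4.9 (difference 2.1), SD 2.8, alpha 0.05 (taken as two-sided), power 80%, ratio 1:1.

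n per arm = 2 × (1.960 + 0.842)² × 2.8² / 2.1² = 2 × 7.85 × 7.84 / 4.41 = 27.9, so 28 per arm and 56 in total, as stated. Then 56 × 1.109 = 62.1, which matches the stated 62. No alpha has been set aside for interim looks. (The 56 reproduces only if SD 2.8 is used for both arms; that is a separate matter and does not affect this point.)

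**4. Error rate if looks could be acted on.** The protocol gives no number of looks, so this is a range. Two-sample t tests were simulated under no difference, with 28 per arm, two-sided 0.05 at each look and 100,000 runs. A false positive is any look with p < 0.05. Simulation error is about 0.1 percentage point, for example √(0.145 × 0.855 / 100,000) = 0.0011.

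| Looks, including the final one | Chance of at least one p < 0.05 |
|---|---|
| 1 | 5.0% |
| 2 | 8.3% |
| 3 | 10.7% |
| 4 | 12.8% |
| 5 | 14.5% |
| 9 (every third pair from the 4th) | 18.5% |
| 24 (every pair from the 5th to the 28th) | 21.6% |

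A cross-check with normal increments and equally spaced looks (400,000 runs) gave 8.3% for 2 looks, 14.2% for 5 and 19.3% for 10. To hold 5% overall with one constant level per look, that level would have to be about 0.029 for 2 looks, 0.016 for 5 and 0.011 for 10.

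**5. Error rate if looks are not acted on.** The only test that counts is the final one, and its level stays at 5%.

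**The case against.** A reader might infer that the plan already breaks both the 5% error rate and the blinding. The documents do not support either claim.

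- **Error rate.** Looking inflates the type I error only if a look can stop or change the trial, or decide what is reported. No section gives such a rule. Criteria for discontinuing {11b} concerns individual patients, and {14} and {20a} describe a single-analysis design. The multiplicity figures therefore describe an exposure. {21a} does not say that each review is a between-arm test at 0.05, and its description of frequency is loose wording, not a testing schedule.
- **Blinding.** Groups are coded, and nothing says that the committee sees results by arm. The adverse events named in {22} are bleeding and pain, which need not identify the arm.
- **Membership.** The committee is not made up of assessors alone; the main researcher also sits on it.
- **Scope.** Bowel symptoms are reported by patients who are not listed as blinded, so a blinded assessor protects these answers less than it protects manometry and palpation.
- **Intent.** Given the safety remit and the answer under {21b}, the mention of effectiveness may be a slip.

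All of this stands as a limit on how strongly the point can be put. It does not remove the contradiction. If the mention is a slip, it should be deleted. If it is intended, the looks must be declared. Nor does the absence of a stopping rule protect the error rate: there is no steering committee ({5d}) and no external monitoring committee ({21a}), while {25} foresees possible changes to outcomes and analyses, and the main researcher would have seen effectiveness data.

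**Conclusion.** The concern holds in a limited form. Sections {17a}, {19}, {21a} and {21b} contradict each other on whether effectiveness is examined during the trial, who does it, and whether those people remain blinded.

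The consequence for blinding is a foreseeable threat, greatest for manometry and anal palpation; no breach is documented. The consequence for the error rate is that it is unprotected. It is 5% if no look is acted on. It would be about 8% with 2 looks, 14% with 5 and 19% to 22% with 10 to 24 if looks could be acted on. These figures assume two-sided tests at an unadjusted 0.05 and a number of looks that the protocol does not give.

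It should be settled before the first patient is enrolled. The Trial status section says that recruitment has not started, so the change can still be made cleanly.

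**What to change.** 1. In {21a}, delete the reference to effectiveness, so that the committee reviews safety only and the answer in {21b} stands.
2. State that no outcome data are compared by arm before the database for the 3-month assessment (T4) is locked. Add that anyone still assessing 1-year (T5) outcomes sees no by-arm results until those assessments are complete. A bar that ended at the T4 lock would leave later T5 assessments exposed.
3. Have safety data by arm reviewed only by existing team members who assess no outcomes, and identify them by role. The protocol does not settle whether the main researcher qualifies: {26a} refers to several main researchers, and {18a} gives outcome assessment to members of the research team. The external surgeon need only be consulted after a reported adverse event, as {21a} already provides.
4. Make the monitoring team in {19} match {21a}, and check both against {17a}.
5. If an effectiveness look is really wanted, declare its number, timing and boundary (for example a single interim look with an O'Brien-Fleming boundary) and amend {21b}.

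Steps 1 to 4 cost wording and a change in who sees which data. The sample size does not change, and no new staff are needed provided that someone on the team assesses no outcomes. The team gives up informal early sight of the results.

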### Adverse event reporting and harms {22}

Possible adverse events might include excessive bleeding or pain. The first will be evaluated with a question asking for the frequency of anal bleeding during the last month (never, once a week or less, twice or three times a week, once a day, many times on a day, continually). In addition, the amount of bleeding will be quantified with the cup measure (less than half a cup, half a cup, more than half a cup, a cup, and so on). They will be assessed immediately after pelvic floor rehabilitation and immediately after pelvic floor pre-rehabilitation. Excessive pain will be determined as a pain equal to or higher than 7 on a visual analog scale from 0 (no pain) to 10 (the worst pain).

### Frequency and plans for auditing trial conduct {23}

Auditing will be conducted only in case the funder or Ethical Committee requires.

### Plans for communicating important protocol amendments to relevant parties (e.g., trial participants, ethical committees) {25}

In case of the need of protocol modifications (e.g., changes to eligibility criteria, outcomes, analyses), we will communicate it to relevant parties (which are the Ethical Committee and trial registry).

### Dissemination plans {31a}

The results of this study will be published at scientific journals and in scientific international/national activities.

## Discussion

This paper presents a protocol for a prospective randomized controlled trial to study the effectiveness of pelvic floor pre(re)habilitation both prior to and after a low anterior resection for rectal cancer, versus no rehabilitation at all, on bowel symptoms, pelvic floor function, and quality of life. There is another similar study protocol published, but as it is a feasibility study, their primary outcome measure is the proportion of eligible patients approached who consented to and attended the educational session. The secondary outcomes included patient compliance, the acceptability of the intervention (assessed using qualitative interviews) and pelvic floor tone, patient bowel function, and quality of life [36]. Besides that, two systematic reviews showed promises of the benefits of PFME on bowel function after rectal cancer. However, the methodological limitations of the included studies justify the need of randomized controlled trials testing the effectiveness of pelvic floor rehabilitation to prevent LARS [11, 12].

This study is innovative because it will include prehabilitation, i.e., a session of pelvic floor physiotherapy prior to the surgery. A possible limitation of this study will be related to oncological results of the included patients, for example if the patient requires adjuvant chemotherapy and have other complications, will delay rehabilitation, which might affect the results. Furthermore, the long follow-up period added to by the social unrest in Chile that started in 2019 and COVID-19 outbreak in early 2020 might increase attrition rates or delay the study results.

The proposed research received ethics approval from Servicio de Salud Metropolitano Oriente [Orient Metropolitan Health Service], Santiago de Chile (approval date: October 08, 2019). Published results are expected in 2022.

## Trial status

Trial recruitment is not started yet due to delays caused by coronavirus pandemics. This is the first protocol version registered on 21 January 2020. We plan to start recruitment by 15 January 2021 and to complete recruitment by 30 December 2022.

## Data Availability

The copy of the booklet for patients will be available upon request to the corresponding author. Data will be available for researchers who provide a methodologically sound proposal for meta-analysis beginning 3 months following the main results’ publication. Data can be obtained by contacting the main researcher. Data will be available by contacting by email the main researcher using details on ANZCTR or trial published articles. Email for requests: [contact] or [contact].

## Abbreviations

CARRET: Cancer of Rectum Rehabilitation Trial
LARS: Low anterior resection syndrome
PFME: Pelvic floor muscle exercises
